### Sample size estimation

The degree of pain reduction was the primary outcome of this study. Data for sample size calculations are based on the change in pain levels at T3, as this is the peak of nitrous oxide effect.Percentage changes in VAS scores ≥ 30% were considered clinically meaningful in settings with large differences in basal pain levels. Based on a set of VAS data we previously collected, the effect size at this time was calculated to be 1.68. We employed PASS 17.0 software to calculate the sample size.To assess the effectiveness of this gas analgesic effect, for the bilateral test, we set α (class I error) to 0.05 and test efficacy 1-β to 90% (β = 0.1).After our calculations, using a two-sided, two-sample equal variance t-test, the ability to reject the null hypothesis of zero effect size with a group sample size of 18(9 cases per group) was 91.67% when the overall effect size was 1.68 and the level of significance (alpha) was 0.05.In order to meet the standards of the State Food and Drug Administration and reduce the inadequacy of this study, we decided to recruit a total of 80 patients(40 cases per group).

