**Method:**

This single-center, randomized, double-blind, and controlled trial will enroll 80 patients. Patients ≥ 18 years of age who underwent rehabilitation 1 month after burn surgery with acute pain (VAS ≥ 4) were included. The main exclusion criteria included: pulmonary disease (pulmonary embolism, pneumothorax), intestinal obstruction, etc. Patients were randomly assigned in a 1: 1 ratio to intervention (A) and control (B) groups. Doctors, therapists, patients, and data collectors were unaware of the assignment outcomes. Rehabilitation will be performed by a therapist. The nurse performing the intervention handed the envelope with the patient code and the A or B assignment to the physician. Group A will receive diluted nitrous oxide inhalation plus conventional therapy (without analgesics) 30 minutes once daily for 4 weeks, and Group B will receive oxygen plus conventional therapy (without analgesics) under the same conditions. Assessments will be performed before the intervention (T0), 2 minutes (T1) and 5 minutes (T2) after the start of the intervention, and 5 minutes (T3) after the start of the intervention. The primary outcome was pain score. Secondary outcomes included vital signs, side effects, quality of life score, scar score, need for adjuvant analgesia, therapist and patient satisfaction, and willingness to receive the same gas again.

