The intervention group will be given diluted nitrous oxide inhalation on the basis of conventional treatment. Prior to the intervention, a trained nurse will inform the patient of the use and precautions of the inhalation valve. Two minutes before rehabilitation training, patients in the intervention group will inhale premixed 65% N2O through a mask with a self-controlled inhalation valve until the end of rehabilitation training; The control group will be given continuous oxygen inhalation. These two gases are inhaled and stopped by a patient-controlled valve to facilitate observation of the state of consciousness (the patient will release the valve when the optimal medication status is reached).The intervention will be performed once daily for 30 minutes for 4 weeks.The conventional treatment approach includes the following aspects: 1. The patient uses drugs as directed by the doctor during hospitalization. 2. Therapist’s psychological counseling to patients before and during operation. Patients in both the intervention and control groups will have continuous blood oxygen saturation and heart rate monitored, and blood pressure will be measured before, during and after the intervention. If an adverse reaction occurs, the inhalation should be stopped immediately and oxygen should be given. The adverse reaction will disappear within a few minutes.

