#### Primary outcome.

The primary outcome was the the degree of pain reduction in patients. Patients’ pain levels will be assessed using the VAS scale at T0 (before intervention), T2 (two minutes after the start of the intervention) and T3 (five minutes after the start of the intervention). VAS allowed subjects to select a point on a straight line 10 cm long (0: painless, 10: worst possible pain) to report their own pain level [17]. The VAS scale is easy to understand and implement, and it is a widely used pain assessment scale, and it does not interrupt the intervention process of subjects. Gas suction starts at T1 and stops at T4.

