### Data management and analysis

In order to ensure the accurate entry of data, two independent personnel enter the data respectively and compare them to ensure consistency. In order to improve quality, researchers are trained before studying. The senior academic statisticians in the group regularly checked the data, including missing values, outliers, etc., and corrected them in time.Missing data from subjects who withdraw from the study will be imputed using multiple imputation methods. Shortly after project initiation, a data monitoring committee (DMC) composition and audit system will be established to monitor data collection and management and patient safety throughout the study. Four professional therapists and nurses, two pain management specialists, and a senior academic statistician who serves as chair of the board will serve as members. Patient safety is monitored and managed by professional therapists and pain management experts.All information will be stored confidentially in the office. Replace all identifying information of the participant, such as name and gender, with a code and always keep it confidential, with only the project manager or attending physician knowing the patient’s personal information. In addition, none of the reports about this study will disclose the personal information of patients.

Statistical analysis will perform using spss.27, with an alpha set at 0.05. The mean (standard deviation), median (interquartile range), minimum value, maximum value and proportion (95% confidence interval) of quantitative data will be listed, and the count data will be described in quantity and percentage. Mean comparison between the two groups will be performed using t-test (normal distribution) and Mann-Whitney test (non-normal distribution). Chi-square test will be used to compare proportions.A value of P < 0.05 will be considered statistically significant.

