Nitrous oxide has shown many advantages in conscious analgesia compared to conventional opioid analgesics. It is an inhaled gas by self-administration and has analgesic, sedative, anxiolytic characteristics. Nitrous oxide has been widely used in recent years, such as dentistry, emergency department, obstetrics and gynecology, pediatrics, postoperative analgesia and other clinical disciplines. It has been reported that a mixture of 20% nitrous oxide and 80% oxygen has an equivalent to 15 mg Comparable analgesic effect of morphine as well as good sedation [23]. It begins to work 30 seconds after inhalation, peaks in two minutes, and the effect disappears within 5 minutes after withdrawal, with mild adverse effects.In addition, it can produce analgesic effects without changing consciousness and cognitive state, which can improve the cooperation of burn patients.

Although nitrous oxide is simple to operate and has mild side effects, it can also be life-threatening in some cases. The replacement of oxygen in the alveoli by nitrous oxide leads to a sudden drop in the partial pressure of blood oxygen, which may lead to hypoxia and asphyxia, which often occurs when the oxygen supply equipment fails and excessive sedation leads to spontaneous respiratory depression. Therefore, it is recommended to use a pre-mixed oxygen/nitrous oxide mixture and monitor with a pulse oximeter. Craniocerebral patients, intestinal obstruction and other patients will have fatal consequences such as cerebral hernia and intestinal perforation. Safety management personnel must strictly grasp the contraindications of nitrous oxide, learn to observe the symptoms of side effects and master first aid measures during training. Diluted nitrous oxide is often stored in cylinders and used through valves to facilitate transportation. Nitrous oxide gas is not expensive, and cylinders and valves can be used repeatedly. Therefore, regular maintenance of equipment and use according to specifications can greatly save costs. Monitoring patients’ vital signs outside surgery is a tricky task. Generally speaking, we can only monitor through portable sphygmomanometers and finger clip oximeters. The disadvantage is that we cannot monitor blood pressure dynamically, but this is enough for the key indicators that need to be monitored.

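### The primary outcome lists pain at both two and five minutes without naming one as primary, and the time labels and the peak-effect reason for T3 contradict each other

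*Protocol article*

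**What the plan says.** All references are to the protocol article.

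- **Primary outcome.** The outcome is the degree of pain reduction, scored by VAS at T0, T2 (two minutes after the intervention starts) and T3 (five minutes after). The section adds: "Gas suction starts at T1 and stops at T4". T2 and T3 have equal standing.
- **Sample size estimation.** "Data for sample size calculations are based on the change in pain levels at T3, as this is the peak of nitrous oxide effect". The calculation is for a single comparison, "using a two-sided, two-sample equal variance t-test", at alpha 0.05.
- **Discussion.** On the time course of the gas: "It begins to work 30 seconds after inhalation, peaks in two minutes".
- **Abstract, Method.** Assessments follow T0 at "2 minutes (T1) and 5 minutes (T2) after the start of the intervention, and 5 minutes (T3) after the start of the intervention".
- **Secondary outcome.** The same T2 and T3 are counted from inhalation rather than from the start of the intervention.
- **Interventions.** "The intervention will be performed once daily for 30 minutes for 4 weeks". Inhalation begins two minutes before training and continues until training ends.
- **Data management and analysis.** "Mean comparison between the two groups will be performed using t-test" if the data are normal, otherwise by a Mann-Whitney test, with P < 0.05 as the criterion. No time point, session or adjustment is attached to this.

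**The concern.** A t-test or Mann-Whitney test takes one value per patient. The article lists two candidate values within a session and describes about 28 treatment sessions (7 × 4), but never says which value enters the test. Model detail can wait for an analysis plan. The primary time point cannot wait in the same way, because the article does address it and its statements conflict. An analysis plan built on this text would inherit the conflict.

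Two things are at stake. First, if the choice between T2 and T3 stays open, either could be reported as the primary result at 0.05, and the real error rate exceeds the nominal one. Second, the only reason given for preferring T3 points, on the article's own pharmacology, to T2. The written rationale therefore cannot be used to settle the choice.

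**Working it through.** **1. The labels side by side**

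| Moment | Abstract | Primary outcome | Secondary outcome |
|---|---|---|---|
| Gas start | no label | T1 | no label |
| 2 min | T1 | T2 | T2, counted from inhalation |
| 5 min | T2 and T3 | T3 | T3, counted from inhalation |
| Gas stop | no label | T4 | no label |

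The label T2 means five minutes in the abstract and two minutes in the outcome sections. T1 is two minutes in one place and gas start in the other. T3 is five minutes in both the abstract and the primary outcome section.

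**2. The clock origin.** Gas starts two minutes before training, and the text does not settle whether the start of the intervention means gas or training.

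| Start means | T2 falls at | T3 falls at |
|---|---|---|
| gas | 2 min of gas, 2 − 2 = 0 min of training | 5 min of gas, 5 − 2 = 3 min of training |
| training | 2 + 2 = 4 min of gas, 2 min of training | 5 + 2 = 7 min of gas, 5 min of training |

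On the gas clock, T2 falls just as training begins and T3 three minutes into it, so the two are not interchangeable measures of pain during training. On neither clock does T3 fall at two minutes of inhalation.

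**3. The plan's own power figure.** Inputs from Sample size estimation: effect size 1.68, 9 per group, two-sided alpha 0.05, equal-variance t-test.

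- Degrees of freedom: 2 × 9 − 2 = 16.
- Noncentrality: 1.68 × √(9/2) = 3.56.
- Noncentral-t power: 91.67%, as stated.

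The arithmetic is right, and it is for one test.

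**4. Two time points, either counting.** Take two standard normal test statistics with correlation ρ under no treatment effect. The type I error is P(|z₁| > 1.96 or |z₂| > 1.96). With independence it is 1 − 0.95² = 9.75%. For correlated statistics it was simulated with 1,000,000 draws per value; ρ is an assumption, since the article gives none.

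| ρ | 0.5 | 0.7 | 0.8 | 0.9 |
|---|---|---|---|---|
| Type I error | 9.1% | 8.3% | 7.8% | 7.0% |

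**5. What a fix does to power.** With 40 per group:

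| Rule | Standardised difference detectable with 90% power | Power at 1.68 |
|---|---|---|
| One test at 0.05 | 0.73 | above 99.9% |
| T2 and T3, each at 0.025 | 0.80 | above 99.9% |

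**The case against.** The best defence is that a time point is indicated. The sample size section names the outcome, takes the change at T3 and sizes one two-sided t-test on it. That stands as far as it goes: T3 is the sizing basis. But it is not declared primary where the outcome is defined, and the reason given for it conflicts with the Discussion.

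The peak conflict may also matter little in practice. The Discussion describes general pharmacology, and because inhalation continues through training the effect could persist from two to five minutes. That softens the consequence but does not reconcile the statements.

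A separate analysis plan may settle session handling and multiplicity, and Fig 1, which holds the assessment schedule, is not available here. This also stands, and it limits the point in three ways:

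- **Testing over 28 sessions.** A reader might infer that pain is compared at each daily session. The text says the gas is given daily; it does not say that VAS is scored or tested daily. If T3 were tested in each of 28 sessions with any one counting, the error would be about 49% to 17% at assumed between-session correlations of 0.5 to 0.9. That describes an analysis the article does not propose.
- **Pooling session records as independent.** This would be invalid, but nothing suggests it is planned; the sizing counts patients.
- **An inconsistent T3.** A reader might infer that T3 itself changes meaning. It is five minutes in both the abstract and the primary outcome section; the conflict lies in T1, T2, the duplicated time and the clock origin.

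Nor is the lack of a mixed model an error in itself. A t-test on one sound value per patient is valid.

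**Conclusion.** The concern holds as a defect in the definition of the primary endpoint. T2 and T3 are both listed and neither is primary; the reason for T3 contradicts the Discussion; the abstract and outcome sections use different labels; and no session or per-patient summary is named.

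The supported size is a type I error of about 7.0% to 9.1% in place of 5%. It rests on two assumptions: that both time points are tested at 0.05 with either counting, a rule the article neither states nor excludes, and that their correlation is between 0.9 and 0.5. Any further inflation across sessions is conditional on VAS being scored and tested at each session. Power is not the problem: the stated figure reproduces, and 40 per group is ample at an effect size of 1.68.

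**What to change.** Settle the following before unblinding:

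1. Use one set of time labels in the abstract, the outcome sections and the schedule, with one clock origin, stating whether it is gas start or training start.
2. Reconcile the peak statements in Sample size estimation and the Discussion.
3. Declare one primary contrast: the between-arm difference in VAS at one named time point (T3 if the sizing basis is kept), adjusted for T0 VAS, for one stated session or one stated per-patient summary, at two-sided 0.05. Make the other time point secondary.
4. If VAS is recorded at every session, a mixed model with a patient random effect, or a per-patient mean, is a suitable way to use all sessions. Session records must not be pooled as independent.

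The cost is wording plus a standard model, with no increase in sample size. One caution applies: averaging over sessions needs no new data only if VAS is already scored at each session. If it is not, naming a single session at which it is scored avoids extra collection.

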### Data management and analysis

In order to ensure the accurate entry of data, two independent personnel enter the data respectively and compare them to ensure consistency. In order to improve quality, researchers are trained before studying. The senior academic statisticians in the group regularly checked the data, including missing values, outliers, etc., and corrected them in time.Missing data from subjects who withdraw from the study will be imputed using multiple imputation methods. Shortly after project initiation, a data monitoring committee (DMC) composition and audit system will be established to monitor data collection and management and patient safety throughout the study. Four professional therapists and nurses, two pain management specialists, and a senior academic statistician who serves as chair of the board will serve as members. Patient safety is monitored and managed by professional therapists and pain management experts.All information will be stored confidentially in the office. Replace all identifying information of the participant, such as name and gender, with a code and always keep it confidential, with only the project manager or attending physician knowing the patient’s personal information. In addition, none of the reports about this study will disclose the personal information of patients.

Statistical analysis will perform using spss.27, with an alpha set at 0.05. The mean (standard deviation), median (interquartile range), minimum value, maximum value and proportion (95% confidence interval) of quantitative data will be listed, and the count data will be described in quantity and percentage. Mean comparison between the two groups will be performed using t-test (normal distribution) and Mann-Whitney test (non-normal distribution). Chi-square test will be used to compare proportions.A value of P < 0.05 will be considered statistically significant.

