#### Secondary outcome.

The patient’s vital signs, including: oxygen saturation, heart rate, blood pressure, will be measured at T0 (before inhalation), T2 (two minutes after inhalation), and T3 (five minutes after inhalation). At the end of the procedure, the subjects will be asked what side effects occurred during the intervention and the consumption of adjunctive analgesics will be recorded. Patient and technician satisfaction and willingness to re-use analgesic gas were also secondary outcomes. Vancouver scar assessment scale and ADL scale were used to observe the scar improvement and functional rehabilitation of patients at T5(Four weeks after intervention), respectively. The purpose of this study is to control acute pain during burn rehabilitation, and the effect of scar treatment is indirect, so scar score and functional improvement are set as secondary outcomes.

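### The normality-driven choice between t-test and Mann-Whitney does not fit the planned multiple imputation, so one pooled result per outcome is not ensured

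*Protocol article*

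**What the plan says.** Two rules stand in the protocol article under Data management and analysis. On missing data: "Missing data from subjects who withdraw from the study will be imputed using multiple imputation methods". On the group comparison: "Mean comparison between the two groups will be performed using t-test (normal distribution) and Mann-Whitney test (non-normal distribution"). The section does not say on which data normality is judged, or how results are combined over imputations.

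The outcome most open to withdrawal is described under Secondary outcome: "Vancouver scar assessment scale and ADL scale were used to observe the scar improvement and functional rehabilitation of patients", rated at T5, after the four-week course of daily sessions. Primary pain is rated two and five minutes after the gas starts.

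Sample size estimation rests on a comparison of means, "using a two-sided, two-sample equal variance t-test".

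**The concern.** Multiple imputation turns one incomplete data set into several completed ones. Its usual combining step needs the same quantity, with a standard error, from each. A t-test supplies that as a mean difference. A Mann-Whitney test supplies a rank statistic and a P value.

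The Mann-Whitney branch is a realistic outcome of the rule, because VAS, scar and ADL scores are bounded and often skewed. Normality is also a property of a particular data set. Once values are imputed, the verdict on normality can differ from one completed data set to the next, and the rule then names two different tests for the same outcome.

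What is at stake is whether each imputed outcome has one result fixed in advance. Without a further decision, which the text does not make, the analyst may hold a set of P values from mixed tests and no stated way to reduce them to one.

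**Working it through.** **1. The plan's own figure.** The inputs are a standardised effect of 1.68, 9 per group and two-sided alpha 0.05, all from Sample size estimation. The noncentrality is 1.68 × √(9/2) = 3.56 on 16 degrees of freedom. The noncentral t distribution gives power 0.9167, which matches the stated 91.67%. With 8 per group power is 87.7%, so 9 is the smallest size reaching 90%. With the planned 40 per group it exceeds 99.9%. The calculation is sound, and it is built on a difference in means.

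**2. What pooling needs.** With m imputations, let Qᵢ be the estimate and Uᵢ its squared standard error in data set i. Rubin's rules give
- pooled estimate = mean of the Qᵢ;
- total variance = mean of the Uᵢ + (1 + 1/m) × B, where B is the variance of the Qᵢ between imputations. For m = 20 the factor is 1.05.

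The t-test supplies Qᵢ and Uᵢ. The Mann-Whitney test as named in the article does not.

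**3. How often the rule names different tests for one outcome.** These settings are assumptions and are not in the article:
- 40 per arm; outcome correlated 0.5 with baseline; values missing at random with probability 5%, 10% or 20%;
- 20 imputations from a normal regression on baseline and arm;
- t-test chosen when Shapiro-Wilk P > 0.05 in both arms of that imputed data set;
- no treatment effect; 600 trials per setting; errors normal or moderately skewed (gamma, shape 4).

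| Assumed missing | Mixed tests, normal | Mixed tests, skewed | At least one Mann-Whitney, normal | At least one Mann-Whitney, skewed |
|---|---|---|---|---|
| 5% | 17.7% | 30.2% | 21.0% | 57.5% |
| 10% | 27.0% | 47.2% | 28.7% | 66.5% |
| 20% | 40.7% | 62.7% | 41.2% | 72.8% |

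Mixed means that some of the 20 data sets go to the t-test and the others to Mann-Whitney. The last two columns add the trials in which all 20 go to Mann-Whitney. In every trial they count, the rule does not deliver a full set of estimates and standard errors.

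**4. Sensitivity to the settings.** Mixed selection at 5%, 10% and 20% missing was:
- effect 0.45, 300 trials per setting: 16%, 28% and 39% (normal); 29%, 50% and 62% (skewed);
- a separate run at effect 0.5: about 22-34%, 33-47% and 41-64%;
- VAS-like scores on 0-10, imputed within arm, with a moderate effect: 13-19%, 24-30% and 34-49%.

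**5. Under one fixed mean comparison.** Every imputed data set gives a mean difference and a standard error, so step 2 applies directly whatever the normality check would have said.

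**The case against.** **A single result is still possible.** Normality could be judged once, for instance on the observed data, or rank-test results could be combined by some other rule. This stands. It is why the point is that one pooled result is not ensured, and it makes the percentages conditional on checking each imputed data set. But the article chooses neither route, and it states both conflicting rules. The conflict is therefore in the text and is more than detail left to a fuller document.

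**The consequences are limited.** The analysts are to be unaware of grouping, the scar and ADL scores are secondary, and a five-minute pain score need not be lost when a patient withdraws later. All of this stands. The article does not say which session supplies the primary score, so the primary outcome may or may not be exposed.

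**Stronger readings that the article does not support.**
- A reader might infer that patients who leave because of side effects will be imputed as if they had tolerated the gas, which would favour nitrous oxide. No imputation model is stated, and a fuller document may hold one. The Interventions section says "If an adverse reaction occurs, the inhalation should be stopped immediately and oxygen should be given"; it does not say that the patient leaves the trial or is no longer rated. Oxygen patients who leave because of pain could bias the result the other way, so neither direction nor size can be given.
- A reader might blame Mann-Whitney for P values that fall on both sides of 0.05 across imputations. In a check at an assumed effect of 0.5 with 20% missing, this occurred in 56% (normal errors) and 59% (skewed) of trials with Mann-Whitney, and in 55% and 59% with the t-test. It reflects variation between imputations under either test. At effect 1.68 it occurred with neither.

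**Conclusion.** The point holds in limited form. The two stated rules do not work together: the Mann-Whitney branch yields nothing that Rubin's rules can pool as a mean difference, and a per-data-set normality check often names different tests for the same outcome. At 40 per arm this affects roughly 20-35% of trials at 5% missing and 40-65% at 20%, with 13% and 34% in the mildest setting tried. These figures rest on assumed withdrawal rates, 20 imputations, Shapiro-Wilk at 0.05 and assumed error shapes.

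The weight falls on the T5 scar and ADL scores. At the planned effect of 1.68 with 40 per group the primary conclusion is not in danger. This is a defect in how the analysis is fixed, and the article does not show a biased treatment effect.

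**What to change.** In Data management and analysis, delete the rule that lets normality choose the test. For each continuous or scale outcome, pre-specify one linear model for the difference in means. Adjust it for the T0 value where one is collected: the baseline list includes pain and the Vancouver score but does not name ADL. Use robust standard errors if the outcome is skewed. Fit the same model in every imputed data set and pool the mean difference and 95% CI by Rubin's rules. Keep Mann-Whitney on the observed data only, as a sensitivity check. This also brings the analysis into line with the mean comparison on which the trial is powered.

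A sensitivity analysis for withdrawals due to side effects or lack of relief is optional.

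The cost is a few sentences and slightly more programming, with no extra patients or visits. The change should be made before unblinding; the article expects analysis to be complete by February 2026.

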### Outcome measures

#### Baseline data.

Demographic data (gender, age, height, weight, country, occupation, etc.) and clinical characteristics (burn site and depth, current pain level, Vancouver scar score) will be recorded for all subjects at T0 (two minutes before intervention). Vital signs, such as blood pressure (BP), heart rate (HR), blood oxygen saturation (SPO2), were also recorded at T0.

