## Limitation

There are indeed some limitations in this study. First of all, the pain score is a subjective result and is susceptible to the subjective influence of patients. Vital signs are objective indicators, but the degree to which they reflect pain varies from person to person. Secondly, there are differences in outcome measures for patients due to differences in the site, degree, and depth of their burns, so we will include patients with similar conditions as much as possible, but cannot completely eliminate this difference.Finally, pain perception is correlated with emotion. Oxygen may produce slight relaxation or euphoria, and even if it does not directly relieve pain, it may indirectly affect the patient’s subjective feelings. Pure oxygen as a placebo may not be a completely inert control, and its effect may lead to an overestimation of the placebo effect and an underestimation of the true analgesic effect of nitrous oxide.

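### The T3 pain change is compared without adjustment for the recorded T0 VAS, and the choice of effect measure is left to the data; one prespecified ANCOVA would be a free improvement

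*Protocol article*

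**What the plan says.** All references are to the protocol article. T3 means five minutes after the start of the intervention, as in the Primary outcome section.

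- **Endpoint.** The Primary outcome section defines it as the "degree of pain reduction in patients", measured by VAS at T0, T2 and T3. The Sample size estimation section adds: "Data for sample size calculations are based on the change in pain levels at T3". It uses a two-sided, equal-variance two-sample t-test.
- **Analysis.** The Data management and analysis section states: "Mean comparison between the two groups will be performed using t-test (normal distribution) and Mann-Whitney test (non-normal distribution". A chi-square test is given for proportions. No covariate or regression model is named.
- **Baseline data.** The Baseline data section says that "clinical characteristics (burn site and depth, current pain level, Vancouver scar score) will be recorded for all subjects at T0".
- **Heterogeneity.** The Sample size estimation section speaks of interpreting VAS changes "in settings with large differences in basal pain levels". The Limitation section accepts that outcomes vary with "differences in the site, degree, and depth of their burns".
- **Design.** The randomization section describes 1:1 allocation and names no stratification factor. The Participants section restricts enrolment to patients with similar burn sites and depths.

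**The concern.** Baseline pain is measured on everyone and described as widely variable, yet the stated comparison uses it at most by subtraction. Subtracting T0 fixes its coefficient at 1, whatever its actual relation to T3. Three things follow.

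1. The estimate may be less precise than the collected data allow.
2. Allocation is not stratified, so a chance difference in T0 pain between groups carries into the observed contrast.
3. The effect measure is not fixed in advance. Roughly normal data give a difference in mean VAS; other data give a rank comparison with no direct reading in cm.

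At stake are the precision and interpretability of the primary estimate, not the validity of the test.

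**Working it through.** **1. The plan's own figure.** Inputs from Sample size estimation: effect size d = 1.68, two-sided alpha 0.05, n = 9 per group. For a two-sample t-test, df = 2n − 2 = 16 and noncentrality = d·√(n/2) = 1.68·√4.5. The exact noncentral t gives power 0.9167, matching the stated 91.67%. With 8 per group it is 0.877, so 9 is the smallest number reaching 90%.

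**2. Power at the planned size.** With n = 40 per group and d = 1.68, unadjusted power exceeds 99.99%. Power is 90% at d of about 0.73 and 80% at about 0.63.

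**3. Precision of ANCOVA against the change score.** Let rho be the T0–T3 correlation and k = SD(T0)/SD(T3). Neither is in the documents, so the values below are assumptions. In units of Var(T3):

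- Var(change) = 1 + k² − 2·rho·k
- Var(ANCOVA) = 1 − rho²
- Var(change) − Var(ANCOVA) = (k − rho)², which is never negative

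Apart from a trivial degree-of-freedom cost, ANCOVA is therefore never less precise, and the gain is zero exactly when k = rho. With k = 1 the variance ratio reduces to (1 + rho)/2. Ratio of ANCOVA to change-score variance:

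| k | rho 0.3 | rho 0.5 | rho 0.7 |
|---|---|---|---|
| 0.5 | 0.96 | 1.00 | 0.93 |
| 0.7 | 0.85 | 0.95 | 1.00 |
| 1.0 | 0.65 | 0.75 | 0.85 |
| 1.3 | 0.48 | 0.54 | 0.59 |

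The standard error falls by 1 − √ratio. For k = 1 this is 19%, 13% and 8%; for k = 0.5 it is 2%, 0% and 4%.

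**4. Chance imbalance.** At 40 per group the difference in mean T0 VAS has standard error √(2/40) = 0.22 SD, so a 95% range of ±1.96 × 0.2236 = ±0.44 SD. With k = 1, an imbalance of 0.44 SD shifts the change contrast by (1 − rho) × 0.44, in the direction that favours the group with higher T0 pain: 0.31, 0.22 and 0.13 SD at rho 0.3, 0.5 and 0.7. ANCOVA removes this shift.

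**5. When the gain would show in power.** At an assumed d = 0.65 on the change scale and k = 1, power at 40 per group is 82% unadjusted, and 95%, 91% and 88% with ANCOVA at rho 0.3, 0.5 and 0.7. At d = 1.68 there is nothing left to gain.

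**6. Choosing the test by distribution.** The article does not say how normality is judged. A Shapiro-Wilk test at 0.05 in either group was assumed and simulated under no effect (20,000 runs, 40 per group). Type I error was 0.052 for normal data and 0.048 for skewed (gamma) data, so there is no material inflation. The rule still switched to Mann-Whitney in about 10% of runs with exactly normal data and about 99% with skewed data. The reported quantity therefore depends on the sample.

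**The case against.** **The sentence is generic, and covariates are often left to an analysis plan.** It does not name the primary outcome. But it is the only method given for comparing quantitative outcomes, and it agrees with the t-test used to size the primary outcome. The unadjusted method is therefore stated, not merely left open. The genericness lowers certainty a little and does not remove the point.

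**The unadjusted analysis is valid and amply powered.** This stands. Under randomisation the unadjusted mean difference is unbiased and both tests are valid; imbalance matters only conditionally on the sample obtained. A reader might infer a biased or inflated primary test, and neither the documents nor the simulation supports that.

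**The gain may be small.** This also stands. T0 precedes both gas and training, while T3 falls during them, so equal variances cannot be taken for granted. A reader might turn the k = 1 figures into a firm saving in patients, but without rho and k the documents do not support one.

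**Burn site and depth are not ignored.** A reader might infer that they are recorded and never used. The Participants section uses both to restrict enrolment. The Limitation section admits this is incomplete, but it narrows what adjustment could still recover, and terms with many levels would cost degrees of freedom in 80 patients.

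**Percentage change.** A reader might take this as the analysed variable and object to its behaviour at low T0. The article uses a 30% change only as a threshold of clinical relevance and sizes the trial on the change at T3.

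**Conclusion.** The point holds as a free improvement. The stated primary comparison is unadjusted although T0 VAS is available for everyone, and its effect measure is not fixed in advance. ANCOVA is at least as precise as the change score, corrects chance imbalance in T0 pain and gives one estimate in cm.

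The standard-error reduction of 19%, 13% or 8% rests on equal T0 and T3 variances and on assumed correlations of 0.3, 0.5 or 0.7. It can be near zero when T0 varies less than T3, for example at k = 0.5 and rho = 0.5, and larger when T0 varies more. At the plan's effect size of 1.68 the trial's conclusion would not change. The benefit to power appears only if the true effect is much smaller, roughly below the 0.73 at which unadjusted power is 90%.

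**What to change.** Before unblinding, replace the distribution-dependent choice for the primary outcome with one prespecified analysis:

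- **Primary:** a linear model (ANCOVA) of T3 VAS on treatment and T0 VAS, reported as an adjusted difference in cm with 95% CI and used whatever the distribution looks like.
- **Sensitivity:** a rank-based or bootstrap version, labelled as such.
- **Optional:** burn site and depth as further covariates in a few prespecified categories, since enrolment already restricts them.
- **Likewise:** adjust the Vancouver scar score at T5 for its T0 value.

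The cost is wording only. All these variables are already scheduled for collection, and neither the sample size nor the visits change.
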